### Interim analyses {21b}

A futility analysis will be performed according to Simon’s method [15]. Enrolment will continue during the futility analysis. The study will be halted if there are fewer than 18 responders (i.e., patients with grade 1 neurotoxicity) in the first 31 patients enrolled in the SLPC arm.

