### Sample size {14}

Simon’s two-stage design [15] will be used. The null hypothesis that the true response rate is 0.60, the proportion of neurotoxicity targeted, will be tested against a one-sided alternative. In the first stage, 31 patients will be accrued. If there are 18 patients or fewer with grade 1 neurotoxicity among these 31 patients in the SLPC arm, the study will be halted. Otherwise, 24 additional patients will be accrued, making a total of 55. The null hypothesis will be rejected if 38 or more responses are observed in 55 of the SLPC arm patients. With a type I error rate of 0.05 and a power of 0.90, 55 patients will be enrolled in each arm, that is to say, 110 patients.

All the previous hypotheses account for a lost-to-follow-up rate at 4 months of 20%.

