### Recruitment {15}

Recruitment is planned over a period of 24 months. The rate of one patient per center per 2 months makes this recruitment target completely achievable.

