## Data collection and management

### Plans for assessment and collection of outcomes {18a}

Motor nerve conduction will be investigated for the median, tibial and fibular nerves, evaluating standard parameters: compound muscle action potential distal latency, baseline-to-negative peak amplitude and area, and motor nerve conduction velocity. Sensory nerve conduction will be recorded for the median, radial, and sural nerves, with sensory action potential peak-to-peak measurement. This EDX protocol will be performed three times for each patient, at the enrolment visit, at M4 (i.e., D1 of the ninth chemotherapy cycle), and at the end of the trial, 28 days after the last dose of SLPC/placebo.

Furthermore, we paired the ONLS questionnaire with the EDX. The ONLS scale is a disability questionnaire with a score that ranges from 0 (no disability) to 12 (severe disability). It has been validated in 100 patients with inflammatory polyneuropathy. It has a strong correlation (r = 0.97) with the Overall Disability Sum Score [14] and is widely used by neurologists assessing peripheral neuropathy.

Patients will complete another questionnaire during the trial, to measure their quality of life: QLQ-C30 version three [16]. Comprising 30 different items (questions), it is made up of 8 multi-item functional (physical, role, emotional, cognitive, and social) and symptom (fatigue, pain, and nausea) scales, one global health status and quality of life (QOL) scale, and 6 single items (dyspnea, insomnia, appetite loss, constipation, diarrhea, and financial difficulties). It covers the majority of the core symptoms recommended for patient-reported outcome measurement in cancer clinical trials [17].

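### Second-stage accrual is described as conditional on stage 1, yet enrolment continues through the roughly 4-month wait for the endpoint, so about 75–83 of 110 patients are randomised when the full stage-1 count is known

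*Protocol article*

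**What the plan says.** Protocol article, Sample size {14}, sets out a sequence. First: "In the first stage, 31 patients will be accrued". Then: "If there are 18 patients or fewer with grade 1 neurotoxicity among these 31 patients in the SLPC arm, the study will be halted". Then: "Otherwise, 24 additional patients will be accrued, making a total of 55". Read plainly, the 24 further SLPC patients enter after the stage-1 result and only if it is favourable. The final rule is: "The null hypothesis will be rejected if 38 or more responses are observed in 55 of the SLPC arm patients".

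Interim analyses {21b} says "Enrolment will continue during the futility analysis" and counts responders "in the first 31 patients enrolled in the SLPC arm". It gives the halt as fewer than 18 responders, whereas Sample size {14} gives 18 or fewer.

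The endpoint is late relative to accrual. Outcomes {12} places it 4 months after the start of the oxaliplatin regimen. Plans for assessment {18a} fixes the visit "at M4 (i.e., D1 of the ninth chemotherapy cycle"). Who will be blinded? {17a} puts randomisation between 30 and 4 days before chemotherapy.

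On speed, Recruitment {15} says "Recruitment is planned over a period of 24 months" and gives one patient per centre every 2 months. There are seven centres (Study setting {9}). Allocation is 1:1 (Sequence generation {16a}). No pause or cap for the wait is stated.

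**The concern.** If enrolment does not stop, the stage-1 count arrives only after part of the second stage has been randomised. The step that Sample size {14} makes conditional then begins before its condition is known. What is at stake is how many patients a futility stop can still spare, and whether the protocol tells its readers that number. Those patients have metastatic cancer, take an ampoule on most days, and have repeated electrodiagnostic examinations. The control of error rates is not at stake.

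**Working it through.** **The plan's own figures.** 31 + 24 = 55 SLPC patients; at 1:1, 2 × 55 = 110 in total. Stage 1 is complete at about 2 × 31 = 62 randomised, and stage 2 is 2 × 24 = 48. If accrual were held, a stop would spare 48. The plan gives no figure for patients randomised at read-out. (At a true rate of 0.60, the rule of at most 18/31 to halt and at least 38/55 to reject has an exact type I error of 0.104, not the stated 0.05. That is a separate matter and does not enter below.)

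**Lag from randomisation to endpoint.** Eight 14-day cycles give 8 × 14 = 112 days to day 1 of cycle 9. Adding 4 to 30 days before chemotherapy gives 116 to 142 days, or 3.8 to 4.7 months.

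**Accrual rate.** The protocol supports two values:
- 110 / 24 = 4.58 per month, the rate needed to meet the target in 24 months
- 7 × 0.5 = 3.5 per month, the stated centre rate

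**Randomised at read-out** = 62 + rate × lag, assuming uniform accrual.

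| | 4.58/month | 3.5/month |
|---|---|---|
| 62nd patient randomised | 62/4.58 = month 13.5 | 62/3.5 = month 17.7 |
| All 31 SLPC results due | month 17.3–18.2 | month 21.5–22.4 |
| Randomised by then | 79–83 | 75–78 |
| Spared by a stop, against 110 | 27–31 | 32–35 |
| Share of the 48 already in | 36–45% | 28–34% |

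Counting 4 calendar months instead of 112 days moves the ranges to 81–85 and 76–80.

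**Expected SLPC size at a true rate of 0.60.** P(at most 18 of 31) = 0.480.
- Accrual held: 55 − 24 × 0.480 = 43.5.
- Accrual continued at 4.58/month (about 39.7–41.7 SLPC at read-out): 0.480 × (39.7 to 41.7) + 0.520 × 55 = 47.7 to 48.6.
- Accrual continued at 3.5/month (about 37.7–39.2 SLPC): 46.7 to 47.4.

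So the range is about 47–49 against 43.5.

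**Effect of early closure.** At most 18 responders among 31 is the same event as at least 13 non-responders among 31. Once the 13th is recorded, no later result can reverse the halt. Given that a halt occurs, the average position of the 13th non-responder (exact negative binomial) is:
- true rate 0.60: SLPC patient 26.8, so 2 × (31 − 26.8) = about 8 fewer randomised
- true rate 0.50: SLPC patient 24.5, so 2 × (31 − 24.5) = about 13 fewer randomised

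If the boundary is fewer than 18, the halt is certain at the 14th non-responder. P(halt at 0.60) is then 0.340, and the gains are about 7 and 10 patients.

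**The case against.** The best defence is that continued enrolment is openly stated and is a normal choice when the endpoint is slow, since the alternative is a pause of about 4 months. That stands. It also stands that overrun does not raise the type I error if the halt is honoured. The protocol regards the product as low risk (Composition of Data Monitoring Committee {21a}), and half of any overrun receives placebo.

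Three stronger readings are tempting and are not supported:
- **Most of the saving is lost.** At 4.58 per month, 27–31 of the 48 are still spared, which is 55–64%.
- **Only 6–9 patients would be spared.** That figure needs recruitment to end at 3.5 × 24 = 84. The planned size is 110, and the gap between 84 and 110 is a separate recruitment problem. A trial ending at 84 could not reach 55 SLPC patients either.
- **The plan requires waiting for all 31 results.** It states a threshold among the first 31 and no timing of looks. Early closure is compatible with its text, and look timing may be set out in documents not shown.

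One might also say that enrolment continues only while the analysis itself is run. Even so, no pause is stated for the endpoint wait, and the two sections still need to agree.

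Against the remedy, it shortens the overrun without removing it. At a true rate of 0.60 and 4.58 per month, about 71–75 patients would still be randomised at an early halt. The gain of 8 applies only when a halt occurs (probability 0.48), so it is about 4 in expectation. A running unblinded count is also a real bias risk: the key is held by the biostatistician and data managers (Implementation {16c}), a biostatistician sits on the Scientific Committee, the data management team sits on the Steering Committee {5d}, and there is no independent committee. This calls for a safeguard but does not defeat the remedy.

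**Conclusion.** The point holds as an inconsistency between Sample size {14} and Interim analyses {21b}, with a moderate cost. About 75–83 of 110 patients are randomised when the full stage-1 count is known. A futility stop spares about 27–35 rather than 48, so roughly 30–45% of the saving is lost. Expected SLPC size at 0.60 rises from 43.5 to about 47–49. These figures assume uniform accrual, 14-day cycles without delay, a stage 1 of the first 31 SLPC patients enrolled, and the boundary in Sample size {14}. The decision to keep enrolling is sound. What needs correcting is the description of stage 2 as conditional, and a halt that is already certain should be acted on at once.

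**What to change.** 1. Keep enrolling, and apply the stage-1 boundary by deterministic curtailment. The key-holding biostatistician tallies recorded non-responders among the first 31 SLPC patients and has randomisation closed once the halt is certain. That is the 13th under the boundary in Sample size {14} and the 14th under that in Interim analyses {21b}; the two boundaries must be reconciled first.
2. State how a missing month-4 grade counts, since 20% loss is expected. The same rule is needed for the full 31-patient count. Recorded non-responders that already reach the boundary make the halt certain whichever rule is chosen.
3. Withhold the tally from the Scientific and Steering Committees until the boundary is met.
4. Reword Sample size {14} so that second-stage accrual is not described as waiting for the stage-1 result, and give the number expected to be randomised when that result is complete (about 75–83 of 110).

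The cost is protocol wording and a running count by someone who already has the allocation. Stop probability, type I error and power are unchanged because the halting event is the same. The small downside is more frequent unblinded counting, which step 3 contains.

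### The stage-1 futility boundary is written two ways, 18 or fewer and fewer than 18 of 31, so the stop/continue decision conflicts at exactly 18

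*Protocol article*

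**What the plan says.** Sample size {14} sets out a Simon two-stage design. "In the first stage, 31 patients will be accrued". The first-stage rule is "If there are 18 patients or fewer with grade 1 neurotoxicity among these 31 patients in the SLPC arm, the study will be halted". The next sentence completes the design: "Otherwise, 24 additional patients will be accrued, making a total of 55". The final rule is "The null hypothesis will be rejected if 38 or more responses are observed in 55 of the SLPC arm patients". The null is "The null hypothesis that the true response rate is 0.60", and it "will be tested against a one-sided alternative", with a type I error of 0.05 and power of 0.90.

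Interim analyses {21b} describes the same futility look, again by Simon's method, in the same arm, on the first 31 patients and with the same responder label (grade 1 neurotoxicity). Its rule is "The study will be halted if there are fewer than 18 responders". It adds that enrolment goes on while the analysis is done.

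**The concern.** A stopping rule has to give one answer for every possible count. The two sentences agree at 17 or fewer (stop) and at 19 or more (continue). At 18 they give opposite instructions. Both sentences are complete, both are current text, and no other section says which prevails. An unseen analysis plan does not remove the problem, because the article fixes the rule itself, in two incompatible ways.

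What is at stake is the go/no-go decision at stage 1. A futility stage exists to stop an inactive product early, and the two readings differ in how often they do so. If the count came out at 18, whoever settled the wording could already know the SLPC-arm result. The section on the Data Monitoring Committee {21a} says that no such committee was set up, so the article names no independent body to rule on it.

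**Working it through.** **Inputs.** From Sample size {14}: n1 = 31, n2 = 24, n = 55, reject at 38 or more, null rate 0.60, one-sided. Stopping rules: X1 ≤ 18 (Sample size {14}) and X1 ≤ 17 (Interim analyses {21b}, where fewer than 18 means 17 or fewer). The article states no alternative rate. I assume 0.80: if 0.60 is the rate free of grade 2 or worse, the complement is 0.40; the 50% decrease in Objectives {7} makes that 0.20, and 1 − 0.20 = 0.80. Rates from 0.60 to 0.80 are shown.

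**Formulas.** With X1 ~ Bin(31, p) and X2 ~ Bin(24, p):
- P(conflict) = P(X1 = 18) = C(31,18) p^18 (1 − p)^13
- P(early stop) = P(X1 ≤ r1), with r1 = 18 or 17
- P(reject) = sum over x from r1 + 1 to 31 of P(X1 = x) · P(X2 ≥ 38 − x)
- Expected SLPC-arm size = 31 + 24 · [1 − P(early stop)]

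**The plan's own figure.** At p = 0.60 with the cut-off of 38 of 55, the type I error is 0.1042 with r1 = 18 and 0.1061 with r1 = 17. The stated 0.05 is reproduced under neither reading. That comes from the final cut-off and is a separate matter; it carries no weight here.

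**Effect of the two readings.**

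| True rate | P(X1 = 18) | Early stop, ≤ 18 | Early stop, ≤ 17 | P(reject), ≤ 18 | P(reject), ≤ 17 |
|---|---|---|---|---|---|
| 0.60 | 0.141 | 0.481 | 0.340 | 0.104 | 0.106 |
| 0.65 | 0.105 | 0.264 | 0.159 | 0.309 | 0.313 |
| 0.70 | 0.054 | 0.107 | 0.053 | 0.615 | 0.621 |
| 0.75 | 0.017 | 0.029 | 0.012 | 0.872 | 0.876 |
| 0.80 | 0.003 | 0.004 | 0.001 | 0.980 | 0.982 |

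At the null the difference in early stopping is 0.4805 − 0.3399 = 0.1406, which is P(X1 = 18), as it must be. In relative terms 0.1406 / 0.4805 = 29% of the early stops are lost under the fewer-than-18 reading.

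Expected SLPC-arm size at the null is 31 + 24 × (1 − 0.4805) = 43.5 with 18 or fewer, and 31 + 24 × (1 − 0.3399) = 46.8 with fewer than 18. Both figures suppose that accrual pauses at 31; since enrolment continues during the analysis, the real saving is smaller under either rule.

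**Why the error rates barely move.** A study that goes on from 18 of 31 needs 38 − 18 = 20 or more responses among the next 24. At p = 0.60 that has probability 0.013. The contribution to type I error is 0.1406 × 0.0134 = 0.0019, which is the gap between 0.1042 and 0.1061.

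**The case against.** The best case against giving this weight is that the inference is almost untouched. Type I error and power each move by about 0.002, and a wrong decision to continue is nearly always corrected by the final test. If the product works as assumed, a count of 18 will hardly ever occur. The intended rule can also be guessed: Sample size {14} holds the full design, and Simon's convention is to stop at r1 or fewer, so the interim section reads like a loose restatement. All of this stands, and it limits the size of the point. It does not remove the contradiction, because an inferable intention is not a written rule.

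A reader might infer more than the article supports:
- **That the two wordings are designs with materially different error rates.** They differ in early stopping near the null, not in type I error or power.
- **That 18/31 is the likeliest borderline count.** At 0.60, 19/31 is slightly more likely (0.144 against 0.141). The count of 18 matters because it is the boundary itself.
- **That, without a monitoring committee, the rule would be chosen after seeing the data.** The article does not say so. The full protocol or an analysis plan, neither shown, could fix the boundary beforehand. The article only leaves room for such a choice.
- **That the denominator must become evaluable patients, or that the analysis plan repeats the error.** The two sections count patients accrued or enrolled. Changing that is a different design decision, and the analysis plan is not at hand.

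**Conclusion.** The point holds as an internal inconsistency in a decision threshold, confined to one stage-1 count. It would decide whether the study stops in about one in seven trials of a product at the null rate (0.141), falling to about one in 60 at a rate of 0.75 (0.017) and three in a thousand at 0.80. The operating characteristic that changes is early stopping at the null, 0.481 against 0.340. The null-rate figures rest only on numbers stated in the article; the power figures rest on the assumed alternative of 0.80 (at 0.75 they are 0.872 against 0.876). It should be corrected because the go/no-go rule must be unambiguous before the interim, not because error control depends on it.

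**What to change.** Before the interim analysis, change the threshold in Interim analyses {21b} from fewer than 18 to 18 or fewer, and leave the rest of that sentence, including its denominator, unchanged. This matches Sample size {14} and Simon's stop-at-r1-or-fewer convention. Alternatively, delete the restated threshold and have Interim analyses {21b} refer to Sample size {14}, so that the rule stands in one place. If the design is recalculated for other reasons, carry its new boundary identically into both sections.

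The cost is a few words in a protocol amendment, with no change to sample size or conduct. The article says that the trial has just started, so at that date there was time to settle the boundary before any stage-1 result was known.

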### Objectives {7}

The primary objective is to demonstrate a 50% decrease in neurotoxicity grades of 2 or above at cycle 9 (4 months after the start of oxaliplatin-based chemotherapy) in the SLPC arm.

The secondary objectives are to compare the following in both arms:➢ Percentage of patients who stopped oxaliplatin due to neurological toxicity➢ Percentage of patients with an oxaliplatin dose decrease➢ Neurological toxicities according to the Common Terminology Criteria for Adverse Events (CTCAE) v5.0➢ Overall toxicity (including hematological toxicity, gastrointestinal toxicity, etc.)➢ Patient’s quality of life according to the EORTC-QLQ-C30 questionnaire

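### The Simon rule counts only grade 1 neurotoxicity as a response, so a patient with no neuropathy is a non-responder, contrary to the grade 2 or above endpoint

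*Protocol article*

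**What the plan says.** Objectives {7} sets the target: "The primary objective is to demonstrate a 50% decrease in neurotoxicity grades of 2 or above at cycle 9". The main analysis in Statistical methods {20a} estimates the prevalence of the same event, grade 2 or above, in each arm.

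The decision rule is worded differently. Sample size {14} gives the null as "The null hypothesis that the true response rate is 0.60, the proportion of neurotoxicity targeted, will be tested against a one-sided alternative". Its first stage reads: "If there are 18 patients or fewer with grade 1 neurotoxicity among these 31 patients in the SLPC arm, the study will be halted". It continues: "Otherwise, 24 additional patients will be accrued, making a total of 55". The final criterion is: "The null hypothesis will be rejected if 38 or more responses are observed in 55 of the SLPC arm patients". Interim analyses {21b} restates the first stage and defines the term, halting if there are "fewer than 18 responders (i.e., patients with grade 1 neurotoxicity) in the first 31 patients enrolled in the SLPC arm".

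No section describes a response as grade 1 or lower, or as grade 0 or 1.

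**The concern.** If the failure event is grade 2 or above, success is everything else: grade 0 or grade 1. Both stage 1 statements leave out grade 0. The background says the supplement is meant to reduce or abolish neuropathy, so the best result for a patient, no neuropathy at all, is not counted as a response. The more patients the supplement moves from grade 1 to grade 0, the lower its response count.

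The statement of the null does not settle the matter. It attaches a neurotoxicity label to the 0.60 response rate, so it does not say plainly which event has probability 0.60.

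Two decisions depend on this definition: the stage 1 halt and the 38-of-55 criterion, the only formal success criterion the article gives for the SLPC arm. The article also states that there is no data monitoring committee, so no such body would catch a literal application.

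**Working it through.** **Inputs from the protocol article.** Stage 1 has 31 SLPC patients and stage 2 adds 24, for a total of 55. The final criterion is at least 38 responses. The null response rate is 0.60, with stated type I error 0.05 and power 0.90 (all Sample size {14}). The stage 1 halt is at 18 or fewer in Sample size {14} and at fewer than 18 in Interim analyses {21b}.

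**Assumption.** The alternative rate is not stated. If 0.60 is the null proportion free of grade 2 or above, then 1 − 0.60 = 0.40 have grade 2 or above. A 50% decrease gives 0.20, so the implied alternative is 1 − 0.20 = 0.80.

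**Formulas.** Let p be the probability that a patient is counted as a responder, and r1 the largest stage 1 count that halts the trial (18 or 17).

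- P(stop) = P(Bin(31, p) ≤ r1)
- P(success) = Σ over x > r1 of P(Bin(31, p) = x) × P(Bin(24, p) ≥ 38 − x)

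**The plan's own figures first.** With r1 = 18, the rule has exact type I error 0.104 at p = 0.60 and power 0.980 at p = 0.80. The stated 0.05 and 0.90 are not reproduced. Raising the final cut-off to 39 gives 0.062 and 0.962; raising it to 40 gives 0.034 and 0.930. This is a separate problem, but it bears on the fix.

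**Effect of the definition.** Hold the share at grade 0 or 1 at 0.80 and vary the part that is grade 0 at cycle 9. Under the literal definition, p = 0.80 − (grade 0 share).

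| Counted as response | Grade 0 share | p | Stop, 18 or fewer | Stop, fewer than 18 | Success |
|---|---|---|---|---|---|
| Grade 0 or 1 | any | 0.80 | 0.004 | 0.001 | 0.980 |
| Grade 1 only | 5% | 0.75 | 0.029 | 0.012 | 0.872 |
| Grade 1 only | 10% | 0.70 | 0.107 | 0.053 | 0.615 |
| Grade 1 only | 20% | 0.60 | 0.480 | 0.340 | 0.104 |
| Grade 1 only | 30% | 0.50 | 0.859 | 0.763 | 0.003 |

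The success column uses the 18-or-fewer halt. Under fewer than 18 it changes by less than 0.01 in every row (for example 0.621 instead of 0.615 at 10%). In the limiting case where every SLPC patient is grade 0, p = 0 and the trial halts with certainty under either cut-off.

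**The case against.** The strongest reply is that the authors almost certainly meant at most grade 1, and that a statistician running the analysis would read it so. That is probably right about intent. But the same wording stands in both places that govern the halt, once as an explicit definition, and nothing in the article corrects it.

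A second reply is that grade 0 will be rare at cycle 9: the Discussion says nearly all patients have some degree of oxaliplatin-induced neuropathy. This stands as a limit on the size. The document gives no grade 0 share at cycle 9, and at 5% the damage is modest. The Discussion's statement is not about patients taking the supplement, however. Stratification by neuropathy stage 0 or 1 does not help either way, since it describes status at randomisation in patients not previously treated with oxaliplatin.

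Third, the final criterion speaks of responses and names no grade. Grade 1 reaches it only by carrying the interim definition over, and the main analysis still estimates the right event. So the effect on the final test is an inference, though a natural one, because no other definition of response is given.

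A reader might go further and infer from "The null hypothesis that the true response rate is 0.60, the proportion of neurotoxicity targeted" that 38 or more of 55 would reward toxicity. The document does not support that. The same sentence speaks of a response rate, and the rule halts for too few responses and rejects for many. The label is loose, but the direction of the test is clear.

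**Conclusion.** The responder definition contradicts the endpoint it serves and must be corrected before the stage 1 look. The direction of the error is certain: counting grade 1 only can only lower the response count and raise the chance of a futility halt. Its size is not known. With 80% free of grade 2 or above, success falls from 0.98 to between 0.87 and 0.003 as the grade 0 share goes from 5% to 30%. The probability of a stage 1 stop runs from 0.03 to 0.86 under the Sample size cut-off, or from 0.01 to 0.76 under the Interim analyses cut-off.

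These figures rest on the inferred 80% and on illustrative grade 0 shares. A reader might conclude that the trial would probably be stopped wrongly. The document does not show that: the grade 0 share may be small, and the likely intent is at most grade 1.

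**What to change.** 1. In Sample size {14} and Interim analyses {21b}, define a responder as a patient with no neurotoxicity of grade 2 or above (grade 0 or 1) at C9D1, and say that the definition applies at both stages.
2. Replace the neurotoxicity label on 0.60 with wording that makes it the null proportion of patients free of grade 2 or above.
3. State the alternative rate. A 50% decrease from 40% implies 0.80, but this is an inference that the sponsor must confirm.
4. Recheck the stated type I error and power against the confirmed rates. With 0.60 and 0.80 the present rule gives about 0.10 and 0.98, so writing those hypotheses in without a recheck would expose a further inconsistency.
5. Reconcile the stage 1 cut-off. The two sections treat exactly 18 responders differently.

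Items 1 and 2 cost a few words and do not touch trial conduct. Items 3 to 5 need a decision by the sponsor and a short recalculation, which may move a cut-off. All should be settled before the stage 1 data are examined.
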